### Sample size calculation

This study will mainly focus on establishing temporal trends in the symptom burden of patients with advanced lung cancer receiving combination immunotherapy and symptom burden in patients with adverse events should be distinguished from that in patients without adverse events. It is estimated that adverse events develop in 30% of patients receiving immunotherapy, and our preliminary research data showed that the symptom score of the patients with adverse events was 1.6 ± 1.1, and the symptom score of the patients without adverse events was 1.0 ± 0.7. According to the t-test of the two groups’ mean and 20% of dropout rate, with a type I error rate of 5% and a power of 90%, using two-sided test, the final sample size is approximately 168 cases.

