### Outcome measures

#### Primary outcome

The primary outcome of this study is the symptom burden in patients with lung cancer during the first-line combination immunotherapy course. It will be assessed using the MDASI-LC and symptomatic irAEs scale directly from patient self-reports. MDASI-LC [17], the lung cancer-specific PRO measurement, will be translated into simplified Chinese to collect longitudinal symptom data once before treatment (typically within 3 days before treatment) and weekly throughout the treatment and till 1 month after treatment completion. It comprises 16 symptoms (pain, fatigue, nausea, disturbed sleep, distress, short breath, remember things, lack of appetite, drowsy, dry mouth, sad, vomiting, numbness, cough, constipation, and sore throat) and six functional items (activity, mood, work, relations, walking, and enjoy life). Each item uses a 0-10-point scale, with 0 representing “symptom has not been present or no functional impairment” and 10 representing “the most severe symptoms or functional impairment”. In addition, the symptomatic irAE scale is a subgroup of symptomatic irAE items from the Patient Reported Outcomes version of the Common Terminology Criteria for Adverse Events library [18, 19], which provides a valid and reliable assessment of symptomatic toxic effects from the patient’s perspective, and is encouraged for use in oncology trials to enhance the accuracy of adverse event reporting [19]. The scale consisting of 15 items (bellyache, diarrhea, bloated pain, night sweats, headache, rash, chills and fever, pruritus, pectoralgia, hemoptysis, abdominal, early satiety, taste change, smell change, and palpitation) will be translated into Chinese to collect the severity score of irAEs. Like the MDASI-LC, it also uses a 0–10 scale, where 0 represents “symptom has not been present or no functional impairment” and 10 represents “the most severe symptoms or functional impairment”.

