### Data analysis

Participants who meet the withdrawal criteria for the study will not be included in the final analysis. For the study results, descriptive analysis will be undertaken by using mean ± SD or median with interquartile range (IQR) for continuous variables, and absolute number (n) and proportion (%) for categorical variables. First, we will use descriptive statistics to describe the severity and time trend of symptom burden and functional interference in patients treated with combination immunotherapy. Symptom trajectories will be depicted with line graphs describing the severity score of patients reporting symptoms from pre-treatment to complete the whole treatment course for 1 month. Furthermore, the association between symptom and clinical outcomes will be examined. Specifically, the symptoms will be categorized based on the severity, and the difference in clinical outcomes (including incidence rate of grade 3–4 immunotoxicity, the completion rate of six cycles of immunotherapy, the timeliness of treatment, complication rate, unplanned clinic rate, OS and PFS) will be assessed. We will use R v.4.2.0 to perform the statistical analysis, and differences will be considered statistically significant if the two-tailed *p*-values are < 0.05.

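### The only stated association analysis cuts the 0–10 symptom scores into severity categories, which loses information that a continuous-score analysis would keep

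*Protocol article*

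**What the plan says.** The Data analysis section first describes symptom severity over time with summary statistics and line graphs, without categories. It then turns to the association with clinical outcomes and specifies the method: "the symptoms will be categorized based on the severity, and the difference in clinical outcomes" will be assessed. The outcomes listed are grade 3–4 immunotoxicity, completion of six cycles, timeliness of treatment, complications, unplanned clinic visits, OS and PFS. No other association method is named. The number of categories, the cut-points and the score to be cut are not given.

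Under Primary outcome, the MDASI-LC is described: "It comprises 16 symptoms" plus six functional items, and "Each item uses a 0-10-point scale". The 15-item irAE scale also runs from 0 to 10.

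The Sample size calculation treats a symptom score as continuous: "the symptom score of the patients with adverse events was 1.6 ± 1.1" and "the symptom score of the patients without adverse events was 1.0 ± 0.7", compared by a t-test.

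**The concern.** If the outcome changes steadily with symptom score, grouping patients treats everyone within a category as alike and discards the differences between them. The estimate becomes less precise and a true association is easier to miss. The result also depends on where the cuts fall.

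The pilot means of 1.0 and 1.6 lie near the bottom of a 0–10 scale, so cuts placed high on the scale could leave few patients above them. What is at stake is the link between symptom burden and clinical outcomes, which the Discussion lists among the study's three potential implications. The description of symptom trajectories, which is the primary outcome, is not affected.

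**Working it through.** **Inputs from the Sample size calculation.** Means and SDs 1.6 (1.1) and 1.0 (0.7); "adverse events develop in 30% of patients receiving immunotherapy", so a 30:70 split; two-sided 5% level; 90% power; 20% dropout; 168 patients.

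**The plan's own figure.** For two means with unequal variances and unequal groups, N = (1.960 + 1.282)² × (1.1²/0.3 + 0.7²/0.7) / 0.6² = 10.51 × (4.033 + 0.700) / 0.36 = 138.2. Rounding up by group gives 42 + 98 = 140, and 140 × 1.2 = 168. The stated figure is reproduced, with the score kept continuous. With 20% dropout, 168 × 0.8 gives about 134 evaluable patients: 40 with and 94 without adverse events.

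**Information kept after categorising.** The share kept is the between-category variance of the score divided by its total variance. This measures the loss for an association that is roughly linear in the score. The score is taken as a 30:70 mixture of the two pilot groups: mean 0.3 × 1.6 + 0.7 × 1.0 = 1.18, SD 0.88. Two shapes were assumed: normal with negative values set to 0, and gamma.

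| Scheme | Normal | Gamma |
|---|---|---|
| Median split | 62% | 52% |
| Tertiles | 78% | 68% |
| Quartiles | 85% | 76% |
| Fixed cuts at 4 and 7 (assumed) | 6% | 23% |
| Fixed cuts at 5 and 7 (assumed) | 1% | 11% |

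Quantile cuts therefore lose between 100 − 85 = 15% and 100 − 52 = 48%. The assumed fixed cuts lose 77% to 99%.

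**How full the upper categories would be, if an average score like the pilot's is cut.** Across normal, gamma, lognormal and beta shapes, 0.6 to 2.1 of 134 patients are expected at or above 4, and fewer than 1 at or above 5. A limit that needs no shape is P(X ≥ c) ≤ σ²/(σ² + (c − μ)²). At c = 4:
- with adverse events: 1.21/(1.21 + 5.76) = 0.174
- without: 0.49/(0.49 + 9.00) = 0.052
- mixture: 0.3 × 0.174 + 0.7 × 0.052 = 0.088, or at most about 12 of 134

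The same limit at 7 is 2.1%, or about 3 patients.

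**How full they would be otherwise.** Low cuts give well-filled groups: under the gamma model about 105 of 134 patients score 0.5 or more, and about 64 score 1 or more. Quantile cuts fill the groups by construction. The remaining cases assume an inter-item correlation of 0.2 to 0.5 and beta-shaped items. An average single item at one time point then has about 4% to 9% of patients at or above 4. If the worst of 16 to 31 items is cut, about 22% to 74% reach 4 and 1% to 29% reach 7.

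**Illustrative power for the adverse-event contrast.** This is simulated with 40 versus 94 patients, gamma scores and a two-sided 5% level. The continuous score (unequal-variance t-test) gives about 92%, or 88% if scores are normal. A median split gives about 70%. Cuts at 1, 2, 3 and 4 give about 76%, 79%, 52% and 14%. The last two depend on the test: an exact test gives about 53% and 14%, and an uncorrected chi-square about 70% and 36%, which is unreliable at such small counts.

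**The case against.** The article condenses a fuller plan. Cut-points, the choice of score and supporting models are commonly left to a statistical analysis plan, and the Discussion speaks of correlation between symptom burden and outcomes. Severity groups also suit the Background's interest in warning signals for intervention. It stands that missing cut-points are no fault of the article. But the article does fix categorisation as the method, and the Discussion names no alternative. An analysis plan that followed this text would supply the cuts and still categorise.

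A reader might infer that the upper categories will be nearly empty wherever the cuts fall. The documents do not support that. It needs fixed cuts high on the scale, applied to an average score like the pilot's, and the article specifies neither. It refers to the symptoms, which could mean single items or a peak over weekly assessments, and it gives no item-level or peak distribution.

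A reader might also infer that categorising erodes the planned 90% power. That power was stated for comparing symptom scores by adverse-event status, not for comparing the seven outcomes across severity groups. The closest listed outcome, grade 3–4 immunotoxicity, is narrower than any adverse event, and OS, PFS and timeliness are different kinds of outcome. The power figures above are therefore illustrative only.

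**Conclusion.** The point holds in limited form. The article commits the association analysis to severity categories and names no continuous analysis. For a graded association this loses information under every scheme tried: about 15% to 48% with quantile cuts, and 77% to 99% with the assumed high fixed cuts on an average score. Sparse upper categories are a risk in that last case only. In the one contrast with pilot data, a median split takes power from about 92% (88% if normal) to about 70%.

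These sizes rest on the pilot means and SDs, the assumed shapes, 134 evaluable patients and a roughly linear relation. If the true relation were a step at the chosen cut, the loss would be smaller. The outcomes concerned are secondary and exploratory. This is a cheap improvement rather than a serious flaw; confidence is moderate.

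**What to change.** In the Data analysis section, make the main association analysis a regression of each clinical outcome on the continuous symptom score. Use a model suited to the outcome type, for example logistic for the yes/no outcomes and Cox for OS and PFS. Report the effect per point or per SD, with a spline check for non-linearity. Keep severity categories for description and display. If categories are kept for testing, state in advance which score is cut and where, and check the expected counts against the pilot data.

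The change is to wording only and needs no new data. The downside is that an effect per point is slightly harder to explain to clinicians than a category; the descriptive tables by severity would cover that.

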## Discussion

Cancer and its treatments often cause multiple symptoms in patients, negatively influencing their prognosis and contributing to physical and psychological consequences [20]. Treatment-related adverse events severely affect prognosis in most cases, and the link between irAEs and prognosis is complicated and related [21]. Although irAEs with delayed onset and prolonged duration are easily neglected [22], organ injury or death resulting from irAEs can have a detrimental effect on patient survival [23], and permanent ICIs cessation due to irAEs can adversely affect treatment benefits [24]. It is therefore evident that symptoms of patients with cancer after treatment with immunotherapy need to be followed up effectively and completely. Electronic patient-reported outcomes (ePROs), which comprise health-related questionnaires completed by the patient themselves, are a promising approach for follow-up and can effectively detect symptoms and their severity. Additionally, as a new follow-up model, it has been reported to be timely and cost-effective and employs a longitudinal collection of patient-symptom data [25] .

Therefore, this study is focused on the assessment of the symptoms following combination immunotherapy, through the application of the ePRO model. Potential implications of the findings include [1] identifying the targeted symptoms for patients with advanced lung cancer receiving first-line combination immunotherapy; [2] demonstrating the longitudinal symptom trajectories of first-line combination immunotherapy for lung cancer; and [3] examining the correlation between symptom burden and clinical outcomes (including incidence rate of grade 3–4 immunotoxicity, the completion rate of six cycles of immunotherapy, the timeliness of treatment, complication rate, unplanned clinic rate, OS and PFS).

ePROs are a novel and significant way to clinically follow up symptoms after treatment with immunotherapy by focusing on patients’ views and experiences. Using this method, this study will help understand symptom trajectories following combination immunotherapy, which is important in improving preparedness for immunotherapy treatment as well as setting up individual strategies to optimize patient experience and outcomes.

## Trial status

Patient recruitment commenced in July 2022 and is currently in progress. This study is planned to be conducted until December 2024.

## Data Availability

No additional data and materials available.

## List of Abbreviations

CTCAE: Common Terminology Criteria for Adverse Events
ePROs: Electronic patient-reported outcomes
irAEs: Immune-related adverse events
ICIs: Immune checkpoint inhibitors
MDASI-LC: MD Anderson Symptom Inventory–Lung Cancer module
OS: Overall survival
PFS: Progression-free survival
PRO: Patient-reported outcome
PROM: patient-reported outcomes measures
SOP: Standard operating procedure
